**Baseline measurements**
Oxygen saturation with pulse oximetry, qualitative dyspnea descriptors, Borg Leg Rating of Perceived Exertion score, and Borg Dyspnea score will be measured before testing.
**Warm-up**
Participants will pedal for 1 minute at a self-selected speed as a warm-up in order to become familiar with the foot peddler.
**Test period**
Participants will continue pedaling at a set speed of 50 revolutions/minute and a resistance setting that allows them to carry on a conversation (approximately 3-4 on the Borg Rating of Perceived Exertion Scale) for as long as they can up to a maximum of 15 minutes. Participants will be prompted every few minutes to monitor their heart rate and oxygen saturation using an oximeter and their Borg Dyspnea score. The test will be stopped based on any of the following stopping criteria:15 minutes have been completed.Oxygen saturation drops to <85%.Self-reported Borg Dyspnea score is >7.The activity becomes unbearable (eg, severe leg pain or the participant is too tired to continue).Heart rate reaches 85% of age-predicted maximum (calculated as 220 beats/minute–age).Participant is unable to maintain a speed of 50 revolutions/minute.The research team member decides to stop the test because of apparent breathlessness or discomfort of the participant.
**Posttest measurements**
The reason for test termination will be recorded, and repeat measurements will be taken for oxygen saturation, qualitative dyspnea descriptors, Borg Leg Rating of Perceived Exertion score, and Borg Dyspnea score. We will also ascertain if participants have any additional comments regarding their test performance.
**Cooldown**
Participants will be instructed to continue pedaling at a self-selected speed and resistance to cool down until heart rate drops to <110 beats/minute.

##### Dual Task Performance

Dual task performance will be evaluated through a dual task test on the foot peddler, as previously undertaken in other populations [46,47]. Participants will complete a motor, cognitive, and combined dual task (all of 1-minute duration) in random order: (1) the *cognitive task* involves spelling 5-letter words backward from a list of 100 words provided verbally (homonyms excluded), (2) the *motor task* involves pedaling on the foot peddler at a set speed of 50 revolutions per minute and a self-selected resistance corresponding to a moderate-intensity level allowing participants to hold a conversation (approximately level 4 on the Borg RPE Scale), and (3) the *dual task* involves spelling and pedaling at the same time. Participants will be instructed to prioritize both tasks equally. Spelling tasks (single and dual tasks) will be audio recorded using a Dictaphone to allow for precise scoring. The number of words correctly spelled backward and the distance covered while pedaling will be compared between the single and dual task conditions to calculate a dual task cost score for both the cognitive and physical performance tasks.

##### Patient-Reported Outcomes

###### Medical Research Council Dyspnea Scale

The Medical Research Council Dyspnea Scale [48] will be used to assess the degree of functional disability because of breathlessness. Participants will indicate the extent to which breathlessness limits their daily physical activities on a scale from 1 (only breathless with strenuous activity) to 5 (too breathless to leave the house or breathless when dressing or undressing).

###### ADL Outcomes

The London Chest Activity of Daily Living scale [49] will be used to assess limitations in performing ADLs because of dyspnea. It comprises 15 questions across 4 domains: self-care, domestic activities, physical activities, and leisure. Each question is rated on a scale from 0 to 5, with 5 representing the greatest dyspnea-related impairment. Total scores range from 0 to 75 points, with higher values indicating greater ADL limitations [50]. The London Chest Activity of Daily Living scale has been applied in patients with COPD with a minimally important difference of 4 points [49].

###### HRQL Outcomes

The St. George’s Respiratory Questionnaire [51] will be administered to measure the impact of COPD on overall health, daily life, and perceived well-being. The questionnaire comprises 50 items. Scores range from 0 to 100, with higher scores indicating worse HRQL. A minimally clinically important difference of 4 points has been identified in patients with COPD [52].

###### Mood

The Depression, Anxiety, and Stress Scale–21 [53] is a 21-item questionnaire that measures the emotional states of depression, anxiety, and stress. It has acceptable to excellent internal consistency and normative data for the COPD population [54]. Scores are categorized as normal, mild, moderate, severe, and extremely severe for each of the 3 domains.

###### Self-Efficacy to Exercise

The Exercise Self-Regulatory Efficacy Scale (Ex-SRES) [55] will be administered to measure exercise self-regulatory efficacy among participants. The Ex-SRES consists of 16 items asking participants to indicate the degree to which they are confident that they could continue to exercise regularly (3 times/week for 20 minutes) when faced with various barriers. Ratings are provided from 0% (not at all confident) to 100% (highly confident). The validity and reliability of the Ex-SRES have been demonstrated in individuals with COPD [55].

##### Physical Activity Levels

The *International Physical Activity Questionnaire–Short Form* [56] will be used to characterize baseline physical activity levels among participants. The International Physical Activity Questionnaire–Short Form consists of 7 questions that capture average time spent sitting, walking, and engaging in moderate and vigorous physical activity over the previous 7 days to provide an estimate of overall activity levels based on metabolic equivalent of task minutes per week.

During the 8-week study period, physical activity levels will be measured via a wrist-worn activity tracker (Fitbit Charge), which will capture daily step count, sedentary time, and number of active minutes (minutes of activity classified as “moderate” or “vigorous” intensity based on heart rate) [57].

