### Study Timeline

The study timeline is shown in Figure 1. After completing consent procedures, participants will receive a package by mail containing the following study equipment: Fitbit Charge 4 device (Fitbit Inc), foot peddler (VANGONA D2 pedal exerciser), pulse oximeter, resistance bands (Thera-Band), measuring tape, and exercise manual. They will also receive an email with instructions on how to access the internet-based appointment platform (Microsoft Teams; Microsoft Corp) on their devices. Following receipt of study materials, participants in both groups will be booked for a 45-minute videoconferencing familiarization session. During the familiarization session, participants will be introduced to the study equipment and software, their safety in performing remote physical testing will be assessed, and study assessment procedures will be explained. Furthermore, appropriate equipment setup for remote testing will be determined, and participants will have the opportunity to practice the physical assessment tests. After the familiarization session, participants will be booked for the *baseline assessment* session (1 hour) to complete the assessment measures described in the following sections.

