### Randomization

After the baseline assessment, participants will be randomized to either the cognitive-physical training (intervention) group or the physical training (control) group using a 1:1 ratio. Randomization will be performed using shuffled opaque envelopes containing the group assignment. Given the pilot stage of this research and the nature of exercise interventions, group allocation will be known to the research team, exercise professionals, and study participants.

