#### Secondary Outcomes

##### Overview

Effect size estimates will be evaluated using secondary outcome measures of physical and cognitive function, dual task performance, ADLs, and HRQL, as described in further detail in the following sections. These measures will be assessed at baseline and at 4 and 8 weeks after starting the intervention. See Table 4 for a summary of secondary outcome measures.

**Table 4 table4:** Secondary outcome measures by time point.

Outcome		Assessment measure	Time points

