**Physical activity**			
	Physical activity habits	International Physical Activity Questionnaire–Short Form	Baseline
	Physical activity behaviors	Fitbit activity tracker	During study period
	Health care use	Medical chart review Self-reported	During study period and 1 year before study enrollment

^a^COPD: chronic obstructive pulmonary disease.

^b^MRC: Medical Research Council.

^c^RPE: Rating of Perceived Exertion.

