#### Data Analysis

Descriptive statistics will be used to summarize recruitment and retention rates, program adherence, participant satisfaction, and safety in both groups. Means and 95% CIs will be reported for the secondary outcomes at baseline, 4 weeks, and 8 weeks within and between groups to derive effect estimates for analysis and sample size calculations for a subsequent larger-scale RCT. Paired 2-tailed *t* tests and 2-tailed *t* tests will be used to compare the changes in the secondary outcome measures over the 8-week study period within and between the 2 randomized groups, respectively. All participants will be included in the analyses based on the intention-to-treat principle according to their group allocation from randomization.

We will explore the contribution of age and sex to feasibility end points and secondary outcomes. Given the modest sample size and importance of age for both cognitive and physical function, we limited our inclusion criteria to the age of ≥50 years to ensure a more homogenous study population. Other important clinical factors such as BMI and medications will be included for descriptive purposes.

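### Fitbit activity has no pre-intervention value, although participants hold the device before randomization, so change from baseline cannot be formed for this secondary outcome

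*Protocol article*

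**What the plan says.** All references are to the protocol article.

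- **Device delivery (Study Timeline):** after consent, "participants will receive a package by mail containing the following study equipment: Fitbit Charge 4 device". The familiarization session follows receipt of the package, and the baseline assessment follows familiarization.
- **Timing of allocation (Randomization section):** "After the baseline assessment, participants will be randomized to either the cognitive-physical training (intervention) group or the physical training (control) group using a 1:1 ratio". Every participant should therefore have the tracker before allocation.
- **Recording window (Physical Activity Levels):** "During the 8-week study period, physical activity levels will be measured via a wrist-worn activity tracker". The variables are daily steps, sedentary time and active minutes. Table 4, the table of secondary outcome measures by time point, has the row "Fitbit activity tracker During study period".
- **Baseline activity (Physical Activity Levels, Table 4):** the only measure is the short-form International Physical Activity Questionnaire (IPAQ), a self-report given once, at baseline.
- **General schedule (Secondary Outcomes, Overview):** "These measures will be assessed at baseline and at 4 and 8 weeks after starting the intervention".
- **Analysis (Data Analysis):** "Means and 95% CIs will be reported for the secondary outcomes at baseline, 4 weeks, and 8 weeks", with paired t tests within groups and two-sample t tests between groups on the changes over eight weeks. No covariate-adjusted model is named.

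**The concern.** The analysis is built on change, but the stated recording window for the only device-measured activity outcome opens when the intervention does. The baseline questionnaire cannot fill the gap. It is expressed in metabolic-equivalent minutes per week from recall, so it cannot be subtracted from steps, sedentary minutes or tracker-defined active minutes, and it is not repeated.

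The first recorded week is no substitute either. Both arms are prescribed aerobic training five days a week, and the tracker classifies active minutes by heart rate, so training sessions can feed directly into the outcome.

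The Data Analysis section says the secondary estimates will serve sample size calculations for a larger trial. Without a pre-randomization value, the pilot cannot supply the SD of change from baseline, or the baseline/follow-up correlation, for device-measured activity. A later analysis plan cannot recover days that were never recorded.

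**Working it through.** **1. Can the planned change be formed?** Setting the sections side by side, the order is: consent, device by mail, familiarization, baseline assessment, randomization, initial training session, eight weeks of training. The activity text places Fitbit recording in the eight weeks. The phrase in Table 4 does not by itself exclude earlier days. However, the health care use row also says during the study period, and the Health Care Use text describes that span as the course of the 8-week intervention, which favours the narrower reading. On that reading no pre-intervention Fitbit value exists.

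**2. Completers.** The Sample Size section gives 12 per group with about 20% attrition: 12 × 0.8 = 9.6, so I use n = 10 per arm. The 12 rests on a cited pilot-study convention, with no SD, effect size or power, so there is no planned precision figure to reproduce.

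**3. What a baseline would be worth.** The correlation ρ between pre-randomization and on-study activity is not in the document. It is an assumption, shown from 0.3 to 0.8. Half-widths of the 95% CI for the between-group difference are in units of the on-study SD, with equal SDs assumed at baseline and follow-up.

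- On-study level only: t(0.975; 18) × √(2/10) = 2.101 × 0.447 = 0.94
- Baseline as covariate (ANCOVA): t(0.975; 17) × √(2/10) × √(1 − ρ²), with t = 2.110
- Unadjusted change score: t(0.975; 18) × √(2/10) × √(2(1 − ρ))

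| ρ (assumed) | Level only | ANCOVA | Versus level only | Change score | Versus level only |
|---|---|---|---|---|---|
| 0.3 | 0.94 | 0.90 | 4% narrower | 1.11 | 18% wider |
| 0.5 | 0.94 | 0.82 | 13% narrower | 0.94 | same |
| 0.6 | 0.94 | 0.75 | 20% narrower | 0.84 | 11% narrower |
| 0.7 | 0.94 | 0.67 | 28% narrower | 0.73 | 23% narrower |
| 0.8 | 0.94 | 0.57 | 40% narrower | 0.59 | 37% narrower |

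Worked line for ρ = 0.6: ANCOVA 2.110 × 0.447 × 0.80 = 0.75; change score 2.101 × 0.447 × √0.8 = 0.84.

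With all 12 per arm the level-only half-width is 0.85 and the ANCOVA percentages are the same to the nearest point. The ANCOVA formula allows for the lost degree of freedom but not for the small extra variance from chance imbalance in the covariate, so its gains are slightly optimistic, most noticeably at ρ = 0.3.

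**4. Chance imbalance.** With 10 per arm, the standard error of a chance difference in habitual activity is √(2/10) = 0.45 SD, so differences up to about 1.96 × 0.45 = 0.88 SD lie within the 95% range. The unadjusted CI already allows for this, but without a baseline the imbalance can be neither seen nor adjusted for.

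**The case against.** The strongest reply is that the Fitbit was never meant for the change analysis. The sentence on baseline, week-4 and week-8 assessment follows a list of physical and cognitive function, dual task performance, activities of daily living and quality of life. Physical activity is not in that list, nor in the aims or hypotheses. Several Table 4 rows are baseline-only, so the general sentence cannot cover every row. The protocol also uses Fitbit data for weekly training review and safety. This reply has force: the mismatch may be loose wording in Data Analysis rather than an intended test. But Table 4 presents the Fitbit as a secondary outcome measure and Data Analysis makes no exception, so the sections need aligning either way.

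Two stronger readings are tempting and are not supported. A reader might infer that no valid Fitbit analysis is possible. That is wrong: randomization makes a between-arm comparison of on-study levels valid without a baseline, and change within the eight weeks can be computed, although it is not change from a pre-intervention value. A reader might also infer that a sizeable precision gain is being given away for nothing. The gain depends on a correlation that the document does not give and on a covariate model that it does not name. Under the planned change-score t test, a baseline would widen the interval for any correlation below 0.5.

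Two practical points also stand. The time from device receipt to randomization is not stated, so the number of usable days is unknown. Software account setup is listed in the training session after randomization, without saying which accounts, so tracker setup might have to move earlier. Finally, the timeline figure is not shown and valid-day rules are often left to a fuller document. The eight-week window, however, is stated in the article itself.

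**Conclusion.** The point holds as a modest, inexpensive improvement to one secondary outcome. As the article is written, Fitbit activity has no pre-intervention value, so the change from baseline that Data Analysis plans for secondary outcomes cannot be formed for it, although the device is available in time.

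Used as a covariate, such a baseline would narrow the between-group CI by about 4% to 40% for assumed correlations of 0.3 to 0.8; at 0.5 the figure is 13%. The conclusion about the missing baseline needs no assumption beyond reading the study period as the eight intervention weeks, whereas the size of the gain rests wholly on the assumed correlation. Recruitment, retention, adherence, safety, satisfaction and the sample size do not depend on it.

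**What to change.** 1. At the familiarization session, set up the tracker and ask participants to wear it until randomization.
2. Define the Fitbit baseline as the mean of valid days before randomization, with a stated minimum number of valid days.
3. Compare on-study activity between arms with that baseline as a covariate, rather than with a simple change score.
4. Reconcile Secondary Outcomes (Overview), Table 4, Physical Activity Levels and Data Analysis. State the Fitbit time points and which secondary measures the change tests cover. If no baseline is recorded, say that Fitbit activity is compared between arms on on-study level only.

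**Cost:** one wear instruction and possibly earlier account setup. Early wear may be affected by novelty, and a short interval before randomization may yield few valid days. Recruitment began in January 2022, so the change can reach only participants not yet randomized. For the others, check whether the device happened to record any days before randomization, and report how many participants have a baseline.

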##### Health Care Use

Health care use over the course of the 8-week intervention and 1 year before study enrollment will be assessed through chart review. The following information will be collected: COPD exacerbation history, history of falls, emergency department visits, admissions to hospital (reasons and length of hospital stay), and mortality during the study period.

### Statistical Procedures

#### Sample Size

A sample size of 12 participants per group is considered appropriate for a pilot study to assess feasibility [58], accounting for an estimated attrition rate of approximately 20% in each group. Power calculations were not performed for the secondary outcomes as the primary study purpose is to assess effect estimates for further program development and evaluation in a future RCT.

#### Data Analysis

Descriptive statistics will be used to summarize recruitment and retention rates, program adherence, participant satisfaction, and safety in both groups. Means and 95% CIs will be reported for the secondary outcomes at baseline, 4 weeks, and 8 weeks within and between groups to derive effect estimates for analysis and sample size calculations for a subsequent larger-scale RCT. Paired 2-tailed *t* tests and 2-tailed *t* tests will be used to compare the changes in the secondary outcome measures over the 8-week study period within and between the 2 randomized groups, respectively. All participants will be included in the analyses based on the intention-to-treat principle according to their group allocation from randomization.

We will explore the contribution of age and sex to feasibility end points and secondary outcomes. Given the modest sample size and importance of age for both cognitive and physical function, we limited our inclusion criteria to the age of ≥50 years to ensure a more homogenous study population. Other important clinical factors such as BMI and medications will be included for descriptive purposes.

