**Methods:**

A total of 24 participants with moderate to severe COPD will be recruited and randomized into cognitive-physical training or physical training. All participants will be prescribed an individualized home physical exercise program comprising 5 days of moderate-intensity aerobic exercise (30-50 minutes/session) and 2 days of whole-body strength training per week. The cognitive-physical training group will also perform cognitive training for approximately 60 minutes, 5 days per week via the BrainHQ platform (Posit Science Corporation). Participants will meet once weekly with an exercise professional (via videoconference) who will provide support by reviewing the progression of their training and addressing any queries. Feasibility will be assessed through the recruitment rate, program adherence, satisfaction, attrition, and safety. The intervention efficacy regarding dual task performance, physical function, ADLs, and HRQL will be evaluated at baseline and at 4 and 8 weeks. Descriptive statistics will be used to summarize intervention feasibility. Paired 2-tailed *t* tests and 2-tailed *t* tests will be used to compare the changes in the outcome measures over the 8-week study period within and between the 2 randomized groups, respectively.

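### Secondary outcomes are compared between arms by unadjusted t tests of change; adjusting for the collected baseline would remove the effect of chance imbalance and, unless the correlation is high, narrow the intervals

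*Protocol article*

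**What the plan says.** The Data Analysis section names two tests for the secondary outcomes, a paired t test and a two-sample t test, both two-tailed. They "will be used to compare the changes in the secondary outcome measures over the 8-week study period within and between the 2 randomized groups", the paired test serving the within-arm question and the two-sample test the between-arm question. The Abstract gives the same plan. The section also promises estimates: "Means and 95% CIs will be reported for the secondary outcomes at baseline, 4 weeks, and 8 weeks within and between groups". Their purpose is "to derive effect estimates for analysis and sample size calculations for a subsequent larger-scale RCT".

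The baseline values are available. Of the secondary measures, the Secondary Outcomes overview says: "These measures will be assessed at baseline and at 4 and 8 weeks after starting the intervention". Table 4 shows this schedule for the physical, cognitive, dual-task and most self-reported outcomes.

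On size and allocation: "A sample size of 12 participants per group is considered appropriate for a pilot study to assess feasibility", allocation is "using a 1:1 ratio", and "Randomization will be performed using shuffled opaque envelopes containing the group assignment". No stratification is described. The Sample Size section allows for about 20% attrition per arm, and the Data Quality and Management section rules out imputation.

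**The concern.** A t test on change scores subtracts the whole baseline value, which amounts to fixing the regression of follow-up on baseline at a slope of 1. With equal SDs at the two visits, the true slope equals the baseline-to-follow-up correlation, which is below 1. Subtracting the whole baseline therefore over-corrects any chance difference between arms at baseline, and unless the correlation is high it also leaves avoidable noise in the estimate. With about ten analysed participants per arm, sizeable chance differences are not rare. This trial supplies one estimate per outcome, and that estimate is meant to inform the design of the next trial.

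The paired tests raise a separate point of interpretation. Both arms follow the same physical program and repeat the same assessments, so improvement may appear in both. A within-arm test cannot isolate what the cognitive training adds. Printing its p value for each arm makes it easy to contrast a significant arm with a non-significant one.

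**Working it through.** **Inputs from the protocol.** There are 12 per arm, and 2 × 12 = 24 agrees with the Abstract: "A total of 24 participants with moderate to severe COPD will be recruited and randomized". With about 20% attrition, 12 × 0.8 = 9.6, or roughly 10 completers per arm. The 12 per arm rests on a cited source with no effect size, SD or power, so it cannot be recomputed, and this point does not depend on it.

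**Assumptions.** The correlation r between baseline and week 8 is not in the documents, so it is varied from 0.3 to 0.95. SDs are taken as equal at the two visits, and results are in units of that SD.

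**1. Chance imbalance.** The baseline difference between arms has SD √(2/n).
- n = 12: √(2/12) = 0.408; P(|difference| > 0.5) = 2Φ(−0.5/0.408) = 0.22.
- n = 10: √(2/10) = 0.447; P(|difference| > 0.5) = 2Φ(−0.5/0.447) = 0.26.

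**2. Effect on the estimate.** Given a baseline difference d, the change-score estimate moves by −(1 − r)d. For d = 0.5 the size is 0.5 × 0.5 = 0.25 SD at r = 0.5, 0.3 × 0.5 = 0.15 SD at r = 0.7, and 0.1 × 0.5 = 0.05 SD at r = 0.9. Simulation (40,000 trials per setting) gave slopes of about −0.50, −0.30 and −0.10 for the change score and about 0 for ANCOVA. Over all randomizations both methods had mean error within 0.002 SD and coverage of about 95%.

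**3. Precision.** Expected 95% CI half-widths:
- Change score: t(2n−2) × √[2(1 − r) × 2/n]
- ANCOVA: t(2n−3) × √[(1 − r²) × (2/n) × (1 + 1/(2n−4))]

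The last factor charges ANCOVA for random baseline imbalance: 1 + 1/16 = 1.0625 at n = 10 and 1 + 1/20 = 1.05 at n = 12. Worked case, n = 10 and r = 0.5: 2.101 × √(1.0 × 0.2) = 0.940, against 2.110 × √(0.75 × 0.2 × 1.0625) = 0.842.

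| r | Change, n = 10 | ANCOVA, n = 10 | Ratio, n = 10 | Ratio, n = 12 |
|---|---|---|---|---|
| 0.3 | 1.112 | 0.928 | 0.835 | 0.828 |
| 0.5 | 0.940 | 0.842 | 0.896 | 0.890 |
| 0.7 | 0.728 | 0.695 | 0.954 | 0.947 |
| 0.8 | 0.594 | 0.584 | 0.982 | 0.975 |
| 0.9 | 0.420 | 0.424 | 1.009 | 1.002 |
| 0.95 | 0.297 | 0.304 | 1.022 | 1.015 |

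Break-even is at r = 0.87 (n = 10) or 0.89 (n = 12). As r approaches 1, the ratio at n = 10 tends to (2.1098/2.1009) × √1.0625 = 1.035, which bounds the expected loss there.

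These are averages. In single simulated trials of 12 per arm, ANCOVA gave the narrower interval in 86% (r = 0.5), 69% (0.7), 57% (0.8) and 40% (0.9).

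**4. Within-arm tests.** Suppose both arms have the same true change, 0.5 SD of the change score (an assumed value). The power p of each paired test is 0.353 at n = 12 and 0.293 at n = 10. The chance that exactly one arm is significant is 2p(1 − p): 2 × 0.353 × 0.647 = 0.46 at n = 12 and 2 × 0.293 × 0.707 = 0.41 at n = 10. There is no arm difference in this setting.

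**The case against.** The strongest reply is that the planned comparison is already sound. It is randomized, unbiased and has correct coverage, so the choice lies between two valid estimators. That stands. A reader might infer that change scores bias the trial's results; the distortion exists only conditionally on the baseline imbalance that happens to occur.

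A second reply is that adjustment is neither free nor always better at this size. That stands too. It spends a degree of freedom and a variance factor of 5% to 6%, and above a correlation of about 0.87 to 0.89 the interval is on average slightly wider. A claim that ANCOVA always narrows the interval would need a correlation that the documents do not supply.

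Third, the Limitations section says the sample is too small to adjust for confounders, naming medications and exacerbations. This does not answer the point: the outcome's own baseline is one covariate, and that passage does not mention it. Exploring age and sex does not replace it.

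Fourth, the protocol never says that efficacy will be judged from one arm's p value. Its hypothesis is comparative, and intervals within and between groups are already promised. This stands: the paired tests are no part of the between-arm estimate, and the risk is one of misreading.

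A reader might also count all the tests and infer a high chance of false positives. The documents do not support such a figure. Within-arm nulls are not expected to hold when both arms train, the tests share data, and baseline adjustment would not change multiplicity.

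**Conclusion.** This is a worthwhile efficiency improvement to a valid secondary analysis. The case rests mainly on chance imbalance: a baseline difference above 0.5 SD has a probability of 22% to 26%, and at an assumed correlation of 0.5 a difference of 0.5 SD moves the planned estimate by 0.25 SD. The precision gain is conditional. At 10 per arm it is about 10% of interval width at correlation 0.5, 5% at 0.7 and 2% at 0.8, turning to a loss of about 1% at 0.9 and 2% at 0.95. These figures assume equal SDs at the two visits, a linear relation with a common slope, and about 10 to 12 analysed per arm. The primary outcomes are feasibility measures summarized descriptively, and nothing here touches them or their success criteria.

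**What to change.** In the Data Analysis section, replace the two-sample t test of change with an ANCOVA of the week-8 value on arm and that outcome's baseline, for each continuous secondary outcome. Report the adjusted difference with its 95% CI, and name it as the basis for effect estimates and for sizing the next trial. Report within-arm change as a mean with 95% CI, without paired-test p values, and state that conclusions about the cognitive training rest on the between-arm estimate.

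No new data are needed. The cost is a change of wording and one degree of freedom per outcome, with intervals about 2% wider if the correlation is as high as 0.95.
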